#### Postoperative acupuncture treatment (second to seventh acupuncture sessions) and acupoint justification

After the operation, the patient will be transferred to the ward after about 1 h. The subject will receive the second acupuncture treatment on the arrival to the ward. Afterwards, the subject will receive an acupuncture treatment every 24 h after the operation in the following 5 days (third to seventh acupuncture sessions). From the second acupuncture session onwards, a combined treatment approach of EA and AA using AA needles will be used.

The treatment procedure of EA, including needling procedure and electric-stimulation parameters, will be the same as the first acupuncture treatment described above, except that only four acupoints will be chosen from the additional acupoints list: GB26, GB34, GB41, HT3, HT7, KI4, KI6, LI11, LR5, LR14, LU7, PC6, SP6, SP14, SP15, SP16, SP21, ST23, ST25, ST27, ST34, CV4, CV12, and EX-CA1 with PC6 as the first choice. After completion of EA, AA will be performed as the first acupuncture treatment mentioned previously, but AA needles will be used. AA needles inserted will be retained and replaced every 3 days until discharge (in case of discharging before day 5) or day 5.

### Sham acupuncture group

To control for the non-specific effects of acupuncture, a non-invasive sham acupuncture method will be performed 1–2 cun away from the true acupoints, where no meridians cross, [32, 33] in the control group.

#### Procedure

To ensure standardization of the needling technique and how we convey to the subjects about “sham acupuncture,” all acupuncture will be performed by the same registered Chinese medicine practitioner. A backup practitioner will also be trained in case the primary practitioner is unavailable.

The acupuncture treatment procedure, including the acupoints selection principle, sterilization procedure, and treatment schedule (treatment time point, duration, and total number of treatments) will be the same as the treatment group except that non-invasive, retractable. sham needles, an inactivated electric stimulator, a non-invasive, sham-acupuncture procedure and dummy auricular intradermal needles will be used on points 1–2 cun away from the true acupoints where no meridians cross [32, 33]. Non-invasive, retractable, sham needles designed by Streitberger will be used [34] for sham EA. The sham needles are blunt needles that will not penetrate the skin during needle insertion. The handles of these sham needles will slide over the needle when it is compressed, giving the appearance of a needle penetrating the skin. The needles are held by surgical tape to imitate the acupuncture procedure. The needles will be connected to an electric stimulator with zero frequency and amplitude. For the sham AA in the first session, a validated sham-acupuncture procedure [35] will be adopted with small modification. A plastic needle-guiding tube will be taped to the points on the auricle to stimulate some discernible sensation. A needle with a piece of adhesive tape will then be immediately applied to the surface of the auricular acupoint [35]. For the sham AA from the second session onwards, dummy auricular intradermal needles with only circular handles will be used. The dummy auricular intradermal needles will be covered by adhesive tape.

### Anesthesia, intraoperative care, and postoperative management

#### Anesthesia

No participant will receive sedative premedication. On arrival in the operating theatre, a 16-gauge intravenous cannula will be inserted under local analgesia. Propofol 2 mg/kg, fentanyl 1.5 μg/kg, and atracurium 0.5 mg/kg will be used for general anesthesia induction. A bolus dose of 0.1 mg/kg morphine sulphate will be given intravenously prior to incision. Pulse, pulse oximetry, and non-invasive blood pressure measurement will be checked every 5 min throughout the operation.

#### Intraoperative care

Anesthesia will be maintained with a mixture of sevoflurane, air, and oxygen. The sevoflurane concentration will be titrated to optimal heart rate and blood pressure by the anesthesiologist ([name] and his team members). At hours 3 and 4, morphine sulphate 0.1 mg/kg may be given in divided dose titrated to the patient’s response.

A thermal blanket and infusion fluid warmer will be used to maintain core body temperature at 35.5 to 37.5 °C. A urinary catheter will be inserted to monitor urine output. An intermittent pneumatic compression device will be applied to the lower limbs for deep vein thrombosis prophylaxis.

At the discretion of the anesthesiologist ([name] and his team members), hypotension will be treated with intravenously administered ephedrine or phenylephrine. Hypertension or tachycardia will be treated with isoflurane up to 2% end-tidal concentration (approximately 1.5 MAC). If persistent, beta-blockers, such as labetalol, or arterial vasodilators, such as hydralazine, may be given. Sevoflurane will be switched off after the closure of the inner layer of the wounds. All participants will have local analgesia infiltrated to their wounds at the end of operation. Reversal will be achieved by intravenously administered neostigmine 50 μg/kg and atropine 20 μg/kg after the operation. The patient will then be transferred to the recovery room for monitoring then to the ward after about 1 h.

#### Postoperative management

All participants will be prescribed paracetamol 1 g every 6 h for 3 days and Celebrex 200 mg twice daily for 3 days. On arrival in the recovery room, boluses of 2 mg of intravenously administered morphine will be given every 5 min until the patient’s NRS pain score is less than 4. The patient will be offered patient-controlled analgesia (PCA). The PCA pump will be configured to give 1 mg of morphine at a time and the lockout duration will be set to 5 min. No basal infusion will be given and the maximum dose limit will be 0.1 mg/kg/h.

From postoperative day 0, rescue analgesic in the form of intramuscularly administered morphine 0.1 mg/kg will be prescribed every 4 h if necessary. During the administration of PCA morphine, the patient will be seen by an anesthesiologist, who is blinded to treatment allocation ([name] and his team members), every day to assess the adequacy of analgesia.

PCA morphine will be administered for at least 2 days. On postoperative day 2, if the participant’s NRS pain score during cough is less than 4 on a clinically low morphine consumption, PCA will be stopped; if the NRS pain score is 4 or above, or her PCA consumption is still high, it will be continued. Assessment will be repeated daily. If a patient’s NRS pain score during a cough remains at 4 or above on day 5, she will be evaluated for complications and managed at the discretion of the anesthesiologist ([name] and his team members).

### Measures

#### Outcome assessment

Subjects will be closely monitored during and after the operation. The primary outcome will be participants’ postoperative pain scores at rest measured by Numerical Rating Scale (NRS) for the first 5 days after operation. The secondary outcomes include postoperative NRS pain scores while coughing; dose and frequency of rescue analgesic use during hospital stay; time to recovery variables; QoR-9, SF-6D, and EQ-5D-5 L. If at any time point after the operation, a participant is unable to be managed according to the protocol for any reason, such as the development of complications, no further data will be collected. Telephone follow-up will be offered for participants discharged before day 5 (Fig. 2).

### Primary outcome measure

#### Pain intensity by Numerical Rating Scale (NRS) at rest

The NRS for pain is a 0–10-point scale with 0 indicating no pain and 10 indicating worst possible pain. NRS pain scores will be measured at rest upon recovery, hourly at 6 h after surgery, then 4-hourly until day 2, 6-hourly until day 3 and then once daily until discharge. The NRS is a commonly used scale for clinical pain research. NRS is chosen because it is easier for patients to grade their pain intensity with numbers and it has been shown to correlate well with the Visual Analog Scale and Brief Pain Inventory as well as other pain measurements [36–39].

### Secondary outcome measures

#### Pain intensity by Numerical Rating Scale (NRS) while coughing

The NRS for pain while coughing will be measured hourly at 6 h after surgery, then 4-hourly until day 2, then 6-hourly until day 3 and then once daily until discharge.

#### Cumulative morphine consumption

Postoperative PCA morphine consumption will be recorded in each participant’s medication log during the hospital stay.

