We hypothesized that acupuncture, as an adjunct treatment, is effective and safe to reduce postoperative pain during the first 5 days following abdominal surgery for gynecological diseases as compared to a sham control. The overall objective of this study is to examine the safety and efficacy of a combined acupuncture treatment of electroacupuncture (EA) and intradermal auricular acupuncture (AA) as an adjunct treatment in reducing postoperative pain in patients after abdominal surgery for gynecological diseases, compared with sham EA in combination with sham AA. Specifically, to test the hypothesis, the objectives of the study are:To determine the efficacy of acupuncture as an adjunct treatment in reducing postoperative pain as measured by the pain Numerical Rating Scale (NRS, the primary outcome) and pain medication consumption during the first 5 days after operation to be calculated as the area under the curve (AUC) to compare the between-group differenceTo determine whether the acupuncture treatment can shorten the time to recovery as measured by time to recovery variables including time to recovery of postoperative bowel functions and food intake; time to ambulation and time to dischargeTo evaluate the safety of acupuncture treatment in postoperative pain in a hospital ward by comparing the number of subjects with adverse events, number of patients withdrawn and reasons of withdrawal in treatment group with the sham control groupTo assess whether acupuncture is cost-effective in improving the postoperative quality of life of patients using the Quality of Recovery-9 (QoR-9), Short Form-6 dimension (SF-6D), and EQ-5D-5 L when compared with sham acupuncture

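### Cumulative morphine consumption counts PCA morphine only, one of three postoperative morphine sources, and the article's sections disagree on its scope, window and summary measure

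*Protocol article*

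**What the plan says.** The secondary outcome headed Cumulative morphine consumption consists of one sentence. It begins "Postoperative PCA morphine consumption will be recorded" and gives the source and period as each participant's "medication log during the hospital stay". No other source is named.

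Postoperative management describes three ways in which a participant receives morphine after surgery:

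- In the recovery room, "boluses of 2 mg of intravenously administered morphine will be given every 5 min" until the NRS score is below 4.
- By PCA, with 1 mg per demand, a 5-minute lockout and a limit of 0.1 mg/kg/h, for at least 2 days.
- From day 0, "rescue analgesic in the form of intramuscularly administered morphine 0.1 mg/kg will be prescribed every 4 h if necessary".

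Intramuscular rescue has its own secondary outcome, which covers dose, frequency and time to first use. Recovery-room morphine appears under no outcome heading.

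The first objective, in the Background, refers to "pain medication consumption during the first 5 days after operation to be calculated as the area under the curve". Statistical analyses compares cumulative morphine between the groups with a *t* test or a Wilcoxon test, mentions no AUC for it, and labels all secondary outcomes exploratory.

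**The concern.** A variable labelled cumulative morphine would be expected to hold all postoperative morphine. As defined, it holds one of three sources that the same article prescribes.

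This matters most for reading the primary result. Resting NRS is measured while morphine is titrated to the pain score and then self-administered. Better analgesia can therefore show as lower NRS, as less morphine, or as both. The morphine total is the natural companion to the NRS AUC, and a partial total is a weaker one. Acupuncture starts before surgery, so an effect could already appear in the recovery-room boluses, which no outcome captures.

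The sections also disagree on what is measured, over which period and in what form. An analyst could follow one section or another and obtain different results.

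**Working it through.** **Plan's own figures.** The article states no expected value, SD or power for cumulative morphine, so there is none to reproduce. The sample size rests on the NRS AUC alone and does reproduce: 3.4 / √((2.9² + 3.6²)/2) = 1.04. At the applied effect size of 0.75, 30 per group gives 81.4% power with the unequal-variance test, and 30/0.85 = 35.3, rounded up to 36 per group. Nothing below changes this.

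**Which sources are counted**

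| Source | In cumulative morphine | In another outcome |
|---|---|---|
| Recovery-room IV boluses | No | No |
| PCA | Yes | – |
| Intramuscular rescue | No | Yes, separately |

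**Three descriptions of the quantity**

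| Section | Scope | Window | Form |
|---|---|---|---|
| Objectives (Background) | Pain medication | First 5 days | AUC |
| Cumulative morphine consumption | PCA morphine | Hospital stay | Cumulative amount |
| Statistical analyses | Cumulative morphine | Not stated | Two-group comparison |

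Pain medication, read literally, also includes the paracetamol and Celebrex prescribed to everyone. The form matters too. An AUC of the dosing rate is simply the total. An AUC of the running total over 5 × 24 = 120 h counts 1 mg given at hour 0 as 120 mg·h and 1 mg given at hour 96 as 120 − 96 = 24 mg·h, a fivefold difference in weight.

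**Size of the uncounted doses.** Body weight is an assumption (50, 60 and 70 kg), and IV and IM milligrams are added one for one.

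- One intramuscular dose = 0.1 × weight = 5, 6 and 7 mg.
- Schedule ceiling at 60 kg: 24/4 × 6 = 36 mg per day.
- Recovery room: 2 mg every 5 min is at most 2 × 60/5 = 24 mg in an hour. For illustration, five boluses are 10 mg.

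These are amounts per patient. The comparison is distorted only by the difference between arms in their mean uncounted dose.

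**Effect on the between-group difference** (acupuncture minus sham)

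Total difference = PCA difference + 0.1 × weight × difference in mean IM doses + difference in mean recovery-room mg.

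The PCA difference is set to −8.33 mg, the 24 h opioid difference quoted in the Background, purely to give a scale. At 60 kg:

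| Difference in IM doses per patient | Difference in recovery-room mg | All-source difference (mg) |
|---|---|---|
| 0 | 0 | −8.33 |
| +0.5 | 0 | −8.33 + 3 = −5.33 |
| 0 | +4 | −8.33 + 4 = −4.33 |
| +1 | 0 | −8.33 + 6 = −2.33 |
| −1 | 0 | −8.33 − 6 = −14.33 |
| −1 | −2 | −8.33 − 6 − 2 = −16.33 |

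The PCA-only figure can overstate or understate the all-source difference.

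**Imbalance needed to cancel the difference through IM doses alone**

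- From 8.33 mg: 8.33/5 = 1.67, 8.33/6 = 1.39 and 8.33/7 = 1.19 doses.
- From 9.14 mg: 9.14/5 = 1.83, 9.14/6 = 1.52 and 9.14/7 = 1.31 doses.

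**The case against.** The best defence is that little is lost. Intramuscular doses are logged over the same stay and reported as a named outcome, so anyone can add them to PCA. The cost analysis includes analgesics, so analgesic use has to be captured somewhere. Reporting PCA and rescue separately is a legitimate choice. Recording through the stay and analysing the first 5 days can coexist as a collection period and an analysis window. The finer rules for summing may sit in a full protocol or SAP that is not shown. The outcome is also declared exploratory.

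Much of this stands. Rescue morphine is recoverable, and the window conflict may be one of wording. What remains is that the article is not silent. It gives the outcome a definition that does not match its label, assigns recovery-room morphine to no outcome, and describes the quantity differently in three sections.

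Three stronger readings are tempting, and the documents do not support them:

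- A reader might infer that the opioid comparison is likely to have the wrong sign. That needs about 1.2 to 1.8 more intramuscular doses per acupuncture patient on average (fewer with a recovery-room difference in the same direction) while that arm uses less PCA. The article gives no rescue rate. If acupuncture works, rescue use would more plausibly fall as well, and PCA-only would then understate the benefit.
- A reader might infer that a patient who moves from PCA to rescue would pass as a responder. Postoperative management continues PCA in patients who still have pain, prescribes rescue alongside it, and such use would appear in the rescue outcome.
- A reader might infer that a shorter stay artificially reduces the total. PCA is given in hospital and stops on pain and consumption criteria. No PCA use is missed after discharge, and a longer stay adds none once PCA has ended.

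**Conclusion.** The point holds as a partial and inconsistently defined secondary outcome. The comparison of cumulative morphine covers one of three prescribed sources and can misstate the size of an opioid difference when the arms differ in the other two. An average imbalance of half an intramuscular dose shifts the difference by 3 mg at 60 kg, against quoted differences of 8.33 to 9.14 mg.

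This rests on assumed weights of 50 to 70 kg, one-for-one addition of IV and IM milligrams, and the pooled differences in the Background serving only as a scale. The article does not say which routes those pooled figures counted. Whether any imbalance will occur is unknown. The outcome is exploratory, and neither the primary NRS comparison nor the sample size is affected.

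**What to change.** Define cumulative morphine as the sum of recovery-room intravenous, PCA and intramuscular rescue morphine, in one stated parenteral-equivalent unit, over one fixed window. The first 5 days would match the objectives. State whether the summary is a total or an AUC, and make the objectives, the outcome definition and Statistical analyses agree. Report the total beside the primary NRS AUC. Keep PCA-only and rescue morphine as components.

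The cost is a few lines of wording and analysis code, plus carrying recovery-room doses into the trial data, since no outcome now collects them. PCA and rescue doses are already in the medication log. No treatment rule, primary analysis or sample size changes, and the outcome stays secondary and exploratory.

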#### Dose and frequency of rescue analgesic (intramuscularly administered morphine) use

The time to first postoperative use, dose, and frequency of rescue analgesic will be monitored and recorded in each subject’s medication log during the hospital stay.

#### Time to recovery variables

The time to recovery of postoperative bowel function and food intake; time to ambulation and time to discharge will be assessed and recorded by physicians during the hospital stay.

#### Quality of Recovery-9 (QoR-9)

The QoR-9 is a nine-item questionnaire, which has been extensively utilized and validated to assess the patients’ quality of recovery after anesthesia [40].

#### Short Form-6 dimension (SF-6D) and EuroQol -5 Dimension-5 Level (EQ-5D-5 L)

Quality of life will be assessed by using a Chinese-translated and validated Medical Outcomes SF-6D and EQ-5D-5 L. The SF-6D and EQ-5D-5 L are a preference-based measure of health (PBMH) for economic evaluation. The SF-6D is composed of six multi-level dimensions, namely, physical functioning, role participation, social functioning, bodily pain, mental health, and vitality, whereas the EQ-5D-5 L has five dimensions for health status description: mobility, self-care, usual activities, pain/discomfort, and anxiety/depression. The SF-6D and EQ-5D-5 L value set [41, 42] for the Chinese population will be used to derive utility scores.

### Side effects associated with opioid use

The occurrence of opioid side effects, including pruritus, sedation, dizziness, nausea, and vomiting and urinary retention, will be accessed.

### Safety assessment

#### Reasons for withdrawal

When a participant withdraws before completing the study, the reasons for withdrawal will be recorded.

#### Adverse events

Adverse events occurring during the study period will be recorded. Vital signs, including heart rate, respiratory rate and blood pressure, will be assessed. The researcher will interview participants using an adverse event record form daily during the hospital stay.

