### Safety analyses

The population for safety analyses will include all participants enrolled in the trial. Participants will be informed the potential adverse events related to acupuncture procedure such as bruises, hematomas, infection, pain, chondritis, during the signing of inform consent. Adverse events will be coded using the *World Health Organization (WHO) Adverse Reaction Terminology Dictionary*. The research assistant will follow-up the participant’s adverse event until it has resolved, subsided, stabilized, or the event is otherwise explained. Special attention will be given to those participants who have discontinued treatment due to adverse events or who experience serious adverse events.

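### The text ties active adverse event finding to the hospital stay and sets no common window, so the between-arm count is biased if length of stay differs by arm

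*Protocol article*

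**What the plan says.** The third objective (protocol article, Background) judges safety "by comparing the number of subjects with adverse events", along with withdrawals and their reasons, in the two arms. It is a count of patients, with no time window attached.

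The section Adverse events opens with a general statement: "Adverse events occurring during the study period will be recorded". The method it then gives is that the researcher will "interview participants using an adverse event record form daily during the hospital stay".

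The section Outcome assessment adds: "Telephone follow-up will be offered for participants discharged before day 5". It refers to Fig. 2 for the schedule. The surrounding paragraph names pain scores, rescue analgesic use, recovery times and quality-of-life measures, but not adverse events.

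The section Safety analyses defines the safety population as everyone enrolled and says how a known event is pursued: "The research assistant will follow-up the participant’s adverse event until it has resolved, subsided, stabilized, or the event is otherwise explained". It names the local reactions that participants are warned of, "such as bruises, hematomas, infection, pain, chondritis". It sets no observation window.

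The second objective asks "whether the acupuncture treatment can shorten the time to recovery", and time to discharge is one of the recovery variables listed there.

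**The concern.** A count of patients with at least one event depends on how long each patient is observed. Here the described observation period ends at discharge, which happens after randomisation and is one of the trial's own outcomes. If one arm goes home earlier, its patients have fewer interview days, and fewer of them will be found to have had an event even when the true daily risk is the same. A real effect on discharge could then be read as a safety advantage.

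This matters most for the treatment under test. Real needles penetrate the skin and auricular needles are retained, whereas the sham needles do neither. A delayed local reaction would therefore be expected mainly in the acupuncture arm. If that arm also leaves earlier, its interviews stop sooner.

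**Working it through.** **What the text fixes.** Four statements bear on ascertainment, and none sets a common window.

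- The study-period statement covers all events but names no way of finding one after discharge.
- The daily interview is an active search, and its length equals the patient's stay.
- The telephone follow-up exists, is offered only to those who leave before day 5, and has no stated adverse event content in the text.
- Pursuing an event to resolution applies to events already found. It does not look for new ones.

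**Inputs.** The article gives 36 patients per arm. It gives no adverse event rate and no length of stay, so there is no figure of its own to reproduce. The rates and stays below are assumptions. Every patient in an arm is given the same stay, and the true rate is the same in both arms.

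**Constant rate.** Proportion found with an event = 1 − exp(−rate × days).

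| Rate per day | 4 days | 5 days | 6 days | 4 v 5: difference | 5 v 6: difference |
|---|---|---|---|---|---|
| 3% | 1 − exp(−0.12) = 11.3% | 1 − exp(−0.15) = 13.9% | 1 − exp(−0.18) = 16.5% | 2.6 points | 2.5 points |
| 5% | 1 − exp(−0.20) = 18.1% | 1 − exp(−0.25) = 22.1% | 1 − exp(−0.30) = 25.9% | 4.0 points | 3.8 points |
| 10% | 1 − exp(−0.40) = 33.0% | 1 − exp(−0.50) = 39.3% | 1 − exp(−0.60) = 45.1% | 6.4 points | 5.8 points |

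The 4 v 5 column applies if the calls do not ask about events. It becomes zero if they do, because both arms are then observed to day 5. The 5 v 6 column applies either way, since the calls cannot shorten the interviewing of those who stay on.

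In patients, 2.6 to 6.4 points of 36 is 0.026 × 36 = 0.9 to 0.064 × 36 = 2.3, so about one or two per arm.

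**Check with a discrete daily risk**, 1 − (1 − p)^days, for 4 v 5 days: p = 5% gives 18.5% v 22.6%, p = 10% gives 34.4% v 41.0%, and p = 20% gives 59.0% v 67.2%. The direction is the same and the sizes are similar. The spurious relative risks are 0.82, 0.84 and 0.88. With 36 per arm, the chance that such a difference reaches significance is 6.2%, 8.2% and 10.7%. For 4 v 6 days it is at most 26%, at p = 20%.

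**Events clustered early.** Suppose the rate is 10% on day 1 and halves each day. The cumulative rate is 0.10 + 0.05 + 0.025 + 0.0125 = 0.1875 by day 4 and 0.1875 + 0.00625 = 0.19375 by day 5. The proportions are 1 − exp(−0.1875) = 17.1% and 1 − exp(−0.19375) = 17.6%, a difference of 0.5 points.

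**The case against.** The strongest reply is that the article does not say ascertainment stops at discharge. It promises to record events over the whole study period and provides telephone contact, and it refers to a schedule that cannot be seen here. What a call asks is also the kind of detail that an article leaves to the full protocol. A reader might infer that events are sought only in hospital and that reactions after discharge are never asked about. The documents do not support that: adverse event questions in the calls can be neither confirmed nor excluded. If they are asked, the imbalance before day 5 largely disappears. It does not disappear for stays beyond day 5.

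A reader might also infer that the trial predicts a shorter stay. It does not. The stated hypothesis concerns pain and safety over the first 5 days. Earlier discharge is a question to be determined, and secondary outcomes are called exploratory. The bias therefore depends on stays actually differing.

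The retained-needle example also has limits. Auricular needles are described as kept until discharge or day 5, so needle exposure is not described as outlasting the stay. Only delayed reactions are in question.

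Finally, a constant daily rate is an unfavourable assumption. The first two sessions fall around surgery and morphine use is reviewed for stopping from day 2, so early clustering is plausible and the artefact could be small. This stands as a limit on the size. It does not affect the direction.

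**Conclusion.** The concern holds in conditional form. The text fixes an active search whose length follows an outcome of the trial, pairs it with a crude count of patients, and states no common window. If length of stay differs between arms, the count is biased towards the arm discharged earlier. If the calls do cover adverse events, this remains true only for stays beyond day 5.

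The size cannot be derived from the article. The 3 to 6 points for one day's difference rests on constant rates of 3% to 10% per day and on uniform stays, both assumed. With early clustering the figure is under 1 point. It should not be read as an expected distortion. At 36 per arm such an artefact would seldom produce a significant test, so what is at risk is the descriptive safety comparison, which is how a trial of 72 patients will mostly be read. The change is worth making because it removes the problem at almost no cost.

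**What to change.** State in the safety section that the between-arm comparison counts patients with at least one adverse event from the first session to the end of postoperative day 5, for every patient whatever the date of discharge. State that the adverse event form used at the bedside is also used at the telephone contacts already planned for patients who go home before day 5. List events found in hospital after day 5 separately, outside that comparison. If Fig. 2 or the full protocol already puts adverse event questions into the calls, only the window and the separate listing need adding.

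The cost is a few minutes per call and a sentence or two in the plan. The small downside is that skin signs reported by telephone are less reliable than a bedside check. Recruitment had already begun, so some patients discharged before the change may have no telephone record. Their number should be reported by arm.
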